### Data Analysis

Linear-mixed models will be conducted to examine the effects of the SAMPLE-PE intervention on the main outcomes of the study (i.e., movement competence development) in the short-term (post-intervention) and medium-term (at follow-up). Separate analyses will be conducted for each outcome measure. Mixed models are used to account for the nested structure of the data. The significance level will be set *p* < 0.05 for all statistical analyses. Regression coefficients for the group variables (with a “0” and “1” dummy coding) will reflect average differences in the outcome variables over time. Potential effects of confounding factors such as sex, age, ethnicity, and deprivation will be examined in the hierarchical linear regression analyses. Mediation analyses will be conducted to examine hypothesized mediating pathways that might explain the expected intervention effects in non-motor (cognitive and affective) domains through gains in actual (Pesce et al., 2016a; Sánchez-López et al., 2019) and perceived movement competence. Attrition analyses comparing children who completed the study and those who dropped out will also be performed. Analyses will be conducted using R and follow an intention-to-treat approach.

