**Methods:**

SAMPLE-PE will be evaluated through a cluster-randomized controlled trial targeting 5–6 year old children from schools located in areas of high deprivation in Merseyside, North-West England. Schools will be randomly allocated to one of three conditions: *Linear Pedagogy*, *Non-linear Pedagogy*, or Control. Non-linear and Linear Pedagogy intervention primary schools will receive a PE curriculum delivered by trained coaches over 15 weeks, while control schools will follow their usual practice. Data will be collected at baseline (T0), immediately post-intervention (T1), and 6 months after the intervention has finished (T2). Children’s movement competence is the primary outcome in this trial. Secondary outcomes include physical activity, perceived competence, motivation, executive functions, and self-regulation. An extensive process evaluation will also examine implementation factors such as intervention context, reach, dose, fidelity and acceptability.

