### Hypotheses

Based on previous literature (Morgan et al., 2013; Tompsett et al., 2017), we expect that children who participate in the *Linear* and *Non-linear* Pedagogy interventions will demonstrate greater improvements in movement competence compared to children following standard PE practice. It is also expected that children in the Non-linear Pedagogy intervention will demonstrate greater movement creativity but lower technical movement proficiency than children in the Linear Pedagogy group (Lee et al., 2014). Furthermore, children in Linear and Non-linear Pedagogy interventions will show greater gains across physical literacy elements (affective [perceived competence and motivation], cognitive [cool executive functions], cognitive-affective [self-regulation] and behavioral [physical activity]) than children in standard PE practice. Finally, it is also expected that the Non-linear Pedagogy intervention will see greater improvements in children’s affective (motivation), cognitive (cool executive functions: cognitive flexibility, working memory, and inhibitory control), cognitive-affective (self-regulation) domains than the Linear Pedagogy intervention (Lee et al., 2014; Alvarez-Bueno et al., 2017; Vazou et al., 2019).

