#### Primary Outcome

##### Movement competence

Movement competence will be assessed through a battery of assessments to examine both technical movement proficiency and movement creativity across different domains (locomotor, object-control, and stability skills). All movement competence assessments will take place during school hours within the school hall or playground and video-recorded for later analysis. Trained research assistants who have established acceptable agreement (80%) in terms of intra-rater and inter-rater reliability with pre-coded videos, will complete analysis of video recordings.

Movement proficiency (technique) will be assessed using the Test of Gross Motor Development-3 (TGMD-3; Maeng et al., 2016) and the Test of Stability Skills (Rudd et al., 2015). Specifically, six locomotor (run, gallop, hop, skip, horizontal jump, slide) and seven object-control (two-hand strike, one-hand strike, one-hand dribble, two-hand catch, kick, overhand throw, underhand throw) skills will be assessed using the TGMD-3 (∼30 min to complete). Proficiency at stability skills will be assessed using the three tasks (log roll, rock, back support) from within the Test of Stability Skills (∼15 min to complete). The psychometric quality of these assessments has been well-established (Rudd et al., 2015; Maeng et al., 2016). Participants will receive a verbal explanation and single demonstration from the assessor and are then given one practice attempt before undertaking two trials of each skill.

Movement creativity will be assessed using the Divergent Movement Ability Assessment (Cleland, 1990), which requires children to complete three stations, a stability skill station, a locomotor skill station and object control skill station (∼15 min to complete). In the stability station, children are asked to make as many shapes on or around the bench as they can. In the locomotor station, children are challenged to find as many different ways to move around the obstacle course as possible. Finally, in the object-control skill station, children will be asked to play with a large ball in a designated area, showing all the different skills and ways that they can play with the ball. For every station, children will complete two 90 s trials, during which, every 30 s the child will get a predefined prompt from the research assistant to support and encourage the child.

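### The primary outcome is a three-instrument battery with no lead score or time point, tested measure by measure at p < 0.05, so the chance of a false-positive primary result is roughly 20–50%, depending on how the plan is read

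*Protocol article*

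**What the plan says.** The abstract of the protocol article states that children's "movement competence is the primary outcome in this trial". The Primary Outcome section opens that term up: "Movement competence will be assessed through a battery of assessments to examine both technical movement proficiency and movement creativity across different domains". Proficiency is covered by two instruments ("Movement proficiency (technique) will be assessed using the Test of Gross Motor Development-3", plus the Test of Stability Skills). For the other construct, "Movement creativity will be assessed using the Divergent Movement Ability Assessment". No composite, lead instrument or primary time point is given.

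Data Analysis sets the testing rule. It plans linear mixed models, addresses post-intervention and follow-up effects, and continues: "Separate analyses will be conducted for each outcome measure". On the error rate: "The significance level will be set *p* < 0.05 for all statistical analyses". It also says that the 0/1 group coefficients represent differences averaged over time.

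The abstract says "Schools will be randomly allocated to one of three conditions". The Hypotheses section expects both pedagogies to beat standard practice on movement competence, and expects that Non-linear children "will demonstrate greater movement creativity but lower technical movement proficiency than children in the Linear Pedagogy group". That makes three contrasts on the primary outcome.

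**The concern.** Under these rules, a significant result on any instrument, for any hypothesised contrast and possibly at either wave, can be reported as a finding on the primary outcome. Nothing in the article ranks the tests or shares the 5% among them.

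The sample size, by contrast, is built on one group-by-time interaction test at 0.05. A reader who sees a 5% level and a single primary outcome would take the trial-wide error to be 5%, and it is not. The Discussion expects implications for the primary school curriculum and for coach and teacher training, so the strength of the headline claim matters.

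**Working it through.** **The plan's own figures.** The article gives no family-wise error rate. Its nearest figure is the sample size for one interaction test at 0.05:
- Correction factor: 1 + (20 − 1) × 0.16 = 4.04.
- 54 × 4.04 = 218.2, stated as 218.
- 218 × 1.2 × 1.2 = 313.9, stated as 314.

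These steps reproduce from 54. The 54 itself does not: with d = 0.4 taken as f = 0.2, three groups, three time points and r = 0.5, 54 children give about 82% power, and 90% needs 67. That is a separate matter. What counts here is that only one test was planned for.

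**Inputs for the error rate**
- Level per test: 0.05 (Data Analysis). Sidedness is not stated; two-sided is assumed.
- Instruments: 3 (Primary Outcome).
- Contrasts: 2 from the group dummies (Data Analysis), or 3 with Non-linear versus Linear (Hypotheses).
- Tests over time: 1 if the coefficient is averaged over time or one wave is used, 2 if T1 and T2 are tested separately. Data Analysis supports either reading.
- Arms: six of 12 schools are headed as control. The split of the other six is not given. Arm weights of 3/3/6 and 4/4/4 were both run.
- Assumed correlations: between instruments 0 to 0.7; between T1 and T2 0.5, the value the sample-size section uses within children.

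**Independent tests.** The chance of at least one false positive among n tests is 1 − 0.95^n.

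**Correlated tests.** I simulated joint normal test statistics under no effect anywhere (400,000 draws), with contrast correlations taken from the shared arms. With weights 3/3/6 the two control contrasts correlate at 0.33; with equal arms, at 0.5. The last column counts only rejections in the hypothesised direction: each pedagogy above control, Linear above Non-linear on the two proficiency instruments, and the reverse on creativity.

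| Reading | Tests | Independent | Correlated, two-sided | Hypothesised direction only |
|---|---|---|---|---|
| 3 instruments × 2 contrasts × 1 | 6 | 26.5% | 19–26% | 10–14% |
| 3 × 3 × 1 | 9 | 37.0% | 25–32% | 15–19% |
| 3 × 2 × 2 waves | 12 | 46.0% | 33–42% | 17–23% |
| 3 × 3 × 2 waves | 18 | 60.3% | 40–51% | 25–31% |

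Raising the T1–T2 correlation to 0.7 lowers the bottom of the 18-test range to 38%.

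**Would naming the scores be enough?** Two co-primary scores with two control contrasts at T1 make four tests: 1 − 0.95^4 = 18.5% if independent, about 15–18% with the same correlations. An adjustment is still needed.

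**The case against.** **An analysis plan may exist, and multiplicity is often settled there.** Had the article said nothing, this would be no finding. But it states the separate-analysis rule and the 0.05 level for every analysis, and it defines the primary outcome as a battery. A later plan that added a hierarchy would have to change those statements. In strict logic, a 0.05 level could be applied to adjusted p-values, but nothing in the article says that it is.

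**The test count is a matter of reading.** This stands. A reader might infer a flat 40–50% error rate, which needs 18 tests. The sentence about coefficients averaged over time, the two group dummies and the single powered interaction all support smaller counts. Only a range is defensible.

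**A pedagogy significantly worse than control is not a success.** This also stands, and the direction-only column reflects it. The matching nominal rate is then 2.5% per test, so 10–31% is still about 4 to 12 times nominal.

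**Adjusting across two different interventions with a shared control is debated.** True. But even one pedagogy against control, on three instruments at one time, gives 1 − 0.95^3 = 14.3% if the tests are independent.

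**Three further inferences are not supported.**
- That the opposite predictions for creativity and proficiency let either arm win. They fix in advance which arm should lead on which construct, and so limit opportunistic reading.
- That every instrument yields domain scores. The Test of Stability Skills is described only as three tasks within one domain.
- That the TGMD-3 alone is the natural primary. The Aims define movement competence as proficiency and creativity.

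**Conclusion.** The point holds as a range. The stated rules put the chance of at least one false-positive primary result at roughly 20–50% two-sided, about 4 to 10 times the nominal 5%: about 19–26% on the narrowest three-instrument reading and about 40–51% on the widest. In the hypothesised direction only, it is about 10–31%.

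The size rests on assumed correlations, an assumed arm split and the choice of reading. The direction of the problem does not: every three-instrument reading tried is well above nominal. The fault lies in what the article fixes, since its primary outcome has no lead test and its alpha rule treats every test alone.

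**What to change.** In Primary Outcome and Data Analysis:

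1. Name one proficiency score (TGMD-3 total) and one creativity score (Divergent Movement total), both at T1, as co-primaries. This matches the definition in the Aims.
2. Apply Holm across the four pedagogy-versus-control tests, with thresholds 0.05/4 = 0.0125, 0.05/3 = 0.0167, 0.05/2 = 0.025 and 0.05.
3. Test Non-linear versus Linear afterwards, and write down the entry condition. A simple valid one is to proceed only if all four tests are rejected, with Holm over the two scores; otherwise report estimates without a confirmatory claim.
4. Label stability, subscales and T2 as secondary, without confirmatory claims.
5. If the family is not narrowed, replace the blanket 0.05 rule with Holm across all movement-competence tests.

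The change needs no new data, but it has two costs.

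- **Power.** As an illustration for one contrast, 90% power at two-sided 0.05 means a standardised effect of 1.960 + 1.282 = 3.242. At 0.0125 the critical value is 2.498, leaving Φ(3.242 − 2.498) = Φ(0.744), about 77%. To restore 90% would take (2.498 + 1.282)² / 3.242² = 1.36 times the sample. Holm recovers some of this after a first rejection. The article's own calculation is for an interaction test at 0.05, so this is only a guide.
- **Timing.** Design schedules T2 for January–February 2019 and the article is dated June 2020. On that timetable the primary would be named after data collection, and the report should say so.

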## Discussion

The SAMPLE-PE study aims to examine the efficacy of two different pedagogical approaches to PE (Linear or Non-linear) upon children living in deprived areas. Each approach is informed by movement learning theories used to support the design of learning experiences which, beyond mere movement learning outcomes, are also tailored to support the development of non-motor (cognitive affective) aspects of children’s physical literacy journey. In this frame of expected outcomes in physical and wider domains, the study also aims at providing important insights into the inter-connected nature of physical, affective and cognitive developments that can be elicited by SAMPLE-PE. To deliver these pedagogical models effectively, the coaches will need to possess an in-depth knowledge of the respective pedagogy and learning design principles to improve movement competence. Coaches will receive a comprehensive and extensive training programme from the research team to enable them to deliver the SAMPLE-PE intervention curriculums. A potential limitation to the evaluation is that we do not have the capacity to examine the fidelity of the training, though we will measure the coaches’ ability to deliver the interventions in accordance with the corresponding pedagogy via direct observation of a sub-sample of PE lessons.

The findings of this study should further develop pedagogical practice, inform learning design within PE, shed new light on how to enhance children’s development of movement competence and, more broadly, lead to a better understanding of how to foster physical literacy in the children who need it most. As such, the study could have significant implications for the primary school PE curriculum and for career professional development and training offered to sports coaches and specialist/generalist primary school teachers. Furthermore, the comprehensive mixed methods process evaluation and use of robust outcome measures should provide novel, inter-disciplinary insight into movement competence as a driver of perceived competence, motivation, cognition and physical activity, and extend current knowledge about the effectiveness of PE interventions. The study has therefore the potential to raise standards and the value of PE, and progress to a scaled-up, effectiveness trial involving classroom teachers in the future.

## Abbreviations

EUPEA: European Physical Education Association
NIH: National Institutes for Health
OECD: Organisation for Economic Co-operation and Development
PE: Physical Education
RCS: Response to Challenge Scale
RCT: Randomized Controlled Trial
SAMPLE-PE: Skill Acquisition Methods fostering Physical Literacy in Early – Physical Education
SDQ: Strengths and Difficulties Questionnaire
STEP, Space: Task, Equipment People
TGMD-3: Test of Gross Motor Development Third Edition
UNESCO, United Nations Educational: Scientific and Cultural Organization.
